# Study plan

## ICU Information Bundle

Relevant information routinely collected during the patient’s ICU admission will be accessed via the ICU clinic information system.

## Initial Survey

Participants will first be provided a series of questionnaires after their standard clinic appointment as described below. The initial survey can be found in Appendix 2.

### Background information

The following questionnaires have been selected to provide information on the patient’s premorbid risk/protective factors and baseline level of function.

The “Metro North Patient Experience Survey – outpatient and community” is an 11-question patient reported experience measure (**PREM**) and will be used to collect information about the participant’s experience during their ICU admission.

The Life Events Checklist (**LEC**) for DSM-5 is a self-report measure designed to screen for potentially traumatic events in a respondent's lifetime. The LEC-5 assesses exposure to 16 events known to potentially result in PTSD or distress and includes one additional item assessing any other extraordinarily stressful event not captured in the first 16 items[20]. There is no formal scoring protocol or interpretation per se, other than identifying whether a person has experienced one or more of the events listed. Respondents indicate varying levels of exposure to each type of potentially traumatic event included on a 6-point nominal scale, and respondents may endorse multiple levels of exposure to the same trauma type. The LEC-5 does not yield a total score or composite score.

The Posttraumatic Adjustment Screen (**PAS**) is a 10-item screening index that has been designed to facilitate the early identification of individuals most at risk for developing PTSD and/or depression following a traumatic injury.

The **General Self Efficacy Scale** is a 10-item psychometric scale that is designed to assess optimistic self-beliefs to cope with a variety of difficult demands in life[21].

The **Patient Employment Information Questionnaire** has been amended from a Questionnaire previously used in epilepsy research and reworded to relate to the patient’s ICU admission. It consists of seven questions around changes to employment and income since their ICU admission.

### PICS Measures

Participants will be invited to complete a suite of carefully selected measures encompassing physical, and psychological function, henceforth referred to as the PICS Measures. As indicated below, some of these measures are collected as part of BAU.

The following research tools have been selected as they have been found to be valid and reliable in this patient cohort and the majority recommended for use in measuring outcomes after ICU admission by an expert group after a DELPHI survey [22]. The research team have beta tested this battery of questions with a control sample, demonstrating that completion takes 13-20 minutes.

The **Hospital Anxiety and Depression Scale (HADS)*** is a questionnaire consisting of two subscales measuring patients’ symptoms of anxiety and depression. Each subscale consists of seven items scored from 0 to 3, resulting in a subscale score range from 0 to 21. A subscale score above 7 suggests clinically significant problems. The questionnaire has been validated among general medical patients as well as critically ill patients [23].

The PTSD Checklist for DSM-5 (**PCL-5**) is a 20-item self-report measure that assesses the 20 DSM-5 symptoms of PTSD. The PCL-5 is a self-report measure that can be completed by patients in a waiting room prior to a session or by participants as part of a research study. It takes approximately 5-10 minutes to complete[24].

The **EQ-5D-5L*** is a standardised, non-disease specific instrument for measuring health-related quality of life and is validated in a critical care population. It consists of a 5-question questionnaire. The five domains assessed are mobility, self-care, usual activities, pain/discomfort, and anxiety/depression[25].

*Collected as part of routine clinic practices and thus not included Appendix 2.

## Post Appointment Questionnaire

To address the primary outcome, the **Post Appointment Questionnaire** is an 8 item self-reported acceptability measure that has been specifically developed for this study. It has been adapted from similar surveys used in previous acceptability studies. Questions focus on whether the participant found their appointment helpful, how confident they feel about managing any psychological symptoms they have or may develop, and how optimistic they feel about their recovery.

## Follow-up Survey

At the 6-month timepoint, participants will repeat the Post Appointment Questionnaire, PICS Measures (including HADS and EQ5D-5L), Life Events Checklist, Generalised Self Efficacy Screen and Patient Employment Information Questionnaire, as well as the Health Services Use Questionnaire described below. The follow-up Survey can be found in Appendix 3.

This **Health Services Use** Questionnaire has 11-items and been adapted from a questionnaire utilised in a recent injury vulnerability study[26]. It explores how often the participant has attended a range of clinical, allied health and alternative health services, whether these services were helpful for their mental health, and for those think they needed more help from health professionals than was accessed, the main reason they didn’t get this help.

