# Aims and objectives

The primary objective of this pilot RCT study is to:

1. To evaluate feasibility (cost and practicability) and acceptability of an early psychiatric intervention in a post-ICU clinic.

Secondary Objectives are:

1. Assess the impact of early psychiatric assessment and provision of referral options on self-efficacy and rates of health service access for patients requiring psychological intervention post-ICU
2. Measure the change in symptom severity for anxiety, depression, and PTSD between presentation, and 6 months after presentation.
3. Measure the impact on work, income, and independence in activities of daily living (ADL)

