# Study procedure

Following verbal consent being provided, participants will be randomised to attend the clinic either when the psychiatrist is present or absent block randomisation in blocks of 4 or 6, in a 1:1 ratio, with the list generated by the study statistician (AB) and provided in enclosed envelopes to conceal allocation until verbal consent is provided. Full written consent will then be obtained when they attend their appointment.

Data will be collected with participant permission from their clinical records and medical history through a data request to ICU data collectors and hospital coders. These data will include demographics, frailty scores, diagnoses and severity of illness, previous mental health history, medications, multidisciplinary interventions, evidence of delirium during their admission and in-hospital complications.

| **Time points** | **Data collected** | |
| --- | --- | --- |
| Discharge from ICU | Contacted by clinical staff about the clinic. | |
| Clinic Appointment | Consent to participate, PICF completed. Routine Hospital Data accessed. Initial survey provided. Randomised to intervention or control arm. | |
|  | Control Group  Standard clinic cares provided as described below. | Intervention Group  Early psychiatric intervention provided as described below, in addition to standard clinic cares. |
| Intervention Follow-up |  | Participant contacted to evaluate response/tolerability of intervention. GP provided further advice as detailed below. |
| 6 Month Follow-up | Participant provides consent to continue participating and completes Follow-up Survey. | |

The timeframe of data collection is summarised in the table below:

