**Conducting an Interview**

1. ICU admission reviewed to understand context, severity of illness and possible ailments.
2. Patient contacted through face to face, telehealth or telephone appointment.
3. Introduction and purpose of interview

Example: *“Thank you for coming in, the clinic runs to provide additional support to patients discharged from ICU. Research is being conducted to help us understand the impact our treatment is having on those surviving ICU admissions.”*

1. Gain confirmation to discuss admission details and conduct assessments.

Example: *“Do you recall your admission in ICU? Would you like me to explain what occurred?”*

If a patient declines and does not wish to talk about admission details, this is respected and staff move onto the assessment phase of the process.

1. Timeline of admission; from origin of admission to discharge. Key points and treatments received (i.e. Intubation, CPR, Medications received, OT, Extubation) are discussed.
2. Assessment form and standardised tools completed (see below):.

Routine Assessments

EQ-5D-5L

HADS

IES-R

Katz index of independence in activities of daily living

Montreal Cognitive Assessment / MOCA – BLIND

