## 6 Month Outcomes Follow-up

At the completion of data collection at the clinic appointment, permission will be sought to contact participants again 6 months after their appointment and participants will be asked to nominate a preferred form of contact.

A member of the research team will contact the participant via their preferred contact method approximately 6 months after their clinic appointment.

After providing consent to continue participating, the participant will complete the outcome measure bundle again.

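### No instrument is assigned to the ADL part of secondary objective 3, and the protocol's one dedicated ADL scale (Katz) is not listed at 6 months

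*Protocol*

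**What the plan says.** Protocol, Aims and objectives, gives the third secondary objective as "Measure the impact on work, income, and independence in activities of daily living (ADL".

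Protocol, Standard Clinic Cares (Conducting an Interview), lists five routine assessments for clinic attenders, among them the "Katz index of independence in activities of daily living". The section on the early psychiatric intervention has participants see the psychiatrist once these standard cares are finished.

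Protocol, PICS Measures, introduces "a suite of carefully selected measures encompassing physical, and psychological function, henceforth referred to as the PICS Measures" and then describes three instruments: HADS, PCL-5 and EQ-5D-5L. Of the last it says: "The five domains assessed are mobility, self-care, usual activities, pain/discomfort, and anxiety/depression".

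Protocol, Background information, describes the Patient Employment Information Questionnaire: "It consists of seven questions around changes to employment and income since their ICU admission".

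Protocol, Follow-up Survey, lists what is repeated at 6 months: the Post Appointment Questionnaire, then "PICS Measures (including HADS and EQ5D-5L), Life Events Checklist, Generalised Self Efficacy Screen and Patient Employment Information Questionnaire", with the Health Services Use Questionnaire added. The schedule table under Study procedure gives for that time point only: "Participant provides consent to continue participating and completes Follow-up Survey". The section 6 Month Outcomes Follow-up says "the participant will complete the outcome measure bundle again" and does not define the bundle.

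Protocol, Statistical analysis, compares the arms on change in the secondary outcomes from baseline to 6 months, by ANCOVA with the baseline result as covariate.

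**The concern.** An objective about impact on ADL, analysed as change to 6 months, needs a named ADL measure taken after the intervention, and a baseline value of the same measure. The protocol names one scale built for ADL, places it before the intervention, and leaves it out of the itemised 6-month list. It assigns no other instrument to the ADL part of the objective.

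What is at stake is whether this part of the objective can be answered with the scale designed for it. This is a matter of data collection, so an analysis plan cannot repair it later: a score that was never taken cannot be analysed. The protocol also stops contact after two unsuccessful attempts at 6 months, which leaves little room to collect a missed scale afterwards.

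**Working it through.** No arithmetic beyond counting applies, and the protocol gives no figure on this point to reproduce. The check sets the objective against the measurement schedule.

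**1. Which instrument serves each part of objective 3?**

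| Part | Instrument | Clinic visit | 6 months |
| --- | --- | --- | --- |
| Work, income | Patient Employment Information Questionnaire | Yes (Initial Survey) | Yes (Follow-up Survey) |
| ADL, dedicated scale | Katz index | Yes (routine assessment) | Not listed |
| ADL-related items | EQ-5D-5L self-care and usual activities | Yes (routine assessment) | Yes (Follow-up Survey) |

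The employment questionnaire is described as covering employment and income only, so it does not supply ADL content. No section links Katz, the EQ-5D-5L or any other instrument to the ADL part.

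**2. Could Katz enter at 6 months under another name?** The Follow-up Survey section comes to 1 (Post Appointment Questionnaire) + 3 (the PICS Measures described) + 1 (Life Events Checklist) + 1 (self-efficacy) + 1 (employment) + 1 (health services use) = 8 instruments. Katz is none of them, and it is not among the PICS Measures. The schedule table adds nothing beyond the survey.

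**3. Are the routine clinic assessments repeated as a set?** The text does not say so. Of the five routine assessments (EQ-5D-5L, HADS, IES-R, Katz and the Montreal Cognitive Assessment), the Follow-up Survey section carries two forward by name, HADS and EQ-5D-5L. The other three, Katz included, are not mentioned there.

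**4. When is Katz taken relative to the intervention?** It belongs to standard cares, and the psychiatrist is seen afterwards. The one planned Katz value is therefore a pre-intervention value in the intervention arm.

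**5. Is that value in the trial dataset?** Not expressly. The clinical-records list under Study procedure names items such as frailty scores, diagnoses and medications, but not Katz. HADS and EQ-5D-5L are flagged as routinely collected study measures; Katz is not.

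**6. Can the planned analysis be run?** ANCOVA needs a 6-month outcome and a baseline covariate. For Katz the planned measurements are one at the clinic visit and none at 6 months, so the model cannot be fitted. For the two EQ-5D-5L items both times exist, so a baseline-adjusted comparison is possible, but the protocol does not designate it as the ADL analysis.

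**The case against.** The strongest reply is that ADL information will exist at 6 months. The EQ-5D-5L is collected in both arms at both times, and self-care and usual activities are ADL content. That stands. A reader might infer from the missing Katz score that the effect on ADL cannot be estimated in either arm, or that none of the ADL outcome is observed. The documents do not support that: they support only that there is no dedicated scale at 6 months and no instrument assigned.

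A second reply is that Katz was never promised as a study outcome. That also stands. It sits among routine assessments beside the IES-R, and for PTSD the trial uses its own PCL-5 instead. The MCID table pairs the EQ-5D with physical function, so the investigators may have meant the EQ-5D-5L to serve the ADL part as well. But the protocol does not say so, and it describes the instrument as one of health-related quality of life.

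A third reply is that item-level or index scoring of the EQ-5D-5L is ordinarily left to the analysis plan. Agreed, and no fault is found on that score; the protocol does not fix how it will be scored. Which scales are collected, and when, is however settled here.

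Finally, Appendix 3 is not shown and the outcome measure bundle is undefined, so Katz could be in either. That possibility remains open. The itemised text does not place it there, and if the appendix does, the two disagree and need aligning.

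**Conclusion.** The point holds in a limited form. Independence in ADL is a stated part of secondary objective 3, no instrument is assigned to it, and the only dedicated ADL scale in the protocol is listed at the clinic visit and not at 6 months. As written, the planned baseline-to-6-month comparison cannot be made on that scale for any of the approximately 30 participants (15 per arm). The only ADL-related data at both times are two of the five EQ-5D-5L domains, which the protocol does not name as the ADL outcome.

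The scope is one of the three components of one of three secondary objectives in a pilot. Work and income are measured at 6 months, and the primary outcome is untouched. It is still worth acting on, because the remedy is cheap before the 6-month contacts take place and largely unavailable afterwards. The conclusion assumes that the Follow-up Survey section lists the survey's contents in full, which cannot be confirmed without Appendix 3.

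**What to change.** Preferred: add the Katz index to the 6-month Follow-up Survey and name it as the ADL outcome for objective 3. The follow-up is already planned in clinic or by phone, and the routine clinic assessment may already be done by telephone. State that the routine-visit Katz value enters the trial dataset as baseline, and analyse the scale by the ANCOVA already specified. The cost is a few minutes per participant, a change to the appendix and an ethics amendment.

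If that burden is not accepted, name the EQ-5D-5L self-care and usual-activities items as the ADL outcome and reword objective 3 to match. This needs no new data collection, but the ADL part then rests on two items of a quality-of-life instrument.

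In either case, define the outcome measure bundle. If Appendix 3 already contains Katz, correct the Follow-up Survey section to agree with it.

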# Study procedure

Following verbal consent being provided, participants will be randomised to attend the clinic either when the psychiatrist is present or absent block randomisation in blocks of 4 or 6, in a 1:1 ratio, with the list generated by the study statistician (AB) and provided in enclosed envelopes to conceal allocation until verbal consent is provided. Full written consent will then be obtained when they attend their appointment.

Data will be collected with participant permission from their clinical records and medical history through a data request to ICU data collectors and hospital coders. These data will include demographics, frailty scores, diagnoses and severity of illness, previous mental health history, medications, multidisciplinary interventions, evidence of delirium during their admission and in-hospital complications.

| **Time points** | **Data collected** | |
| --- | --- | --- |
| Discharge from ICU | Contacted by clinical staff about the clinic. | |
| Clinic Appointment | Consent to participate, PICF completed. Routine Hospital Data accessed. Initial survey provided. Randomised to intervention or control arm. | |
|  | Control Group  Standard clinic cares provided as described below. | Intervention Group  Early psychiatric intervention provided as described below, in addition to standard clinic cares. |
| Intervention Follow-up |  | Participant contacted to evaluate response/tolerability of intervention. GP provided further advice as detailed below. |
| 6 Month Follow-up | Participant provides consent to continue participating and completes Follow-up Survey. | |

The timeframe of data collection is summarised in the table below:

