**Participants and sample calculation:**

Data will be collected from a sample of approximately 30 patients attending the Redcliffe ICU follow-up clinic over a 12-month period, with 15 randomised to the control and intervention arms respectively.

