## Sampling and recruitment

Patients attending the Redcliffe Post-ICU clinic will be informed about the trial of an inclusion of an early psychiatric review as part of the clinic following their completion of standard clinic cares (see Appendix 1 for the Standard Operating Procedures).

If the patient expresses interest in the study, they will be provided written and verbal information regarding the purpose and aims of the study and invited to ask any questions they have about the study before being invited to participate. Potential participants will not be aware if they have been randomised to the control or intervention arm at this stage.

The potential participant will be provided multiple opportunities to discuss the study with members of staff not involved in the study. Information will be provided in writing and verbally before the patient is invited to consent to participate in the study.

A patient information and consent form will be provided. People who agree to participate will complete the written consent form before any data collection takes place. Patients who consent to participate will be randomised using a simple randomisation schedule. Participants randomised to the intervention arm will be offered an appointment with the psychiatrist in addition to standard clinic cares, whereas participants randomised to the control arm will receive standard clinic cares only.

For those attending their appointment over the phone, verbal consent will be obtained and witnessed. People who give consent will give permission for research staff to access data from their clinical records and will complete a series of questionnaires examining their premorbid function, experiences in ICU and their subsequent recovery across a range of domains.

To monitor recruitment, a re-identifiable log will be kept that will document patients eligible for approach, and subsequent contact.

Participants will be able to withdraw from the study at any time. If a participant that has been randomised to receive the early psychiatric intervention chooses to withdraw consent, they will receive the standard cares provided by the clinic without the intervention, and any collected data will be withdrawn from the study.

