**Consent:**

All potential participants will receive information about the study in writing and verbally and have the opportunity to ask any questions they have and discuss their participation with a person of their choosing should they wish. Potential Participants will be allowed as much time as they need to consider participation, and participants can decline assessments or withdraw from further participation at any time.

The research team decided for simple randomisation prior to consent for the following reasons:

Minimise departure from standard practice for participants not participating in the study.

In BAU, patients are not invited to the post-ICU clinic while still in ICU, and this is instead discussed several weeks after discharge to allow some time for rest and recovery prior. Informed consent while still in hospital would require participants to make a decision about the post-ICU clinic much earlier in their recovery trajectory than usual.

Respect the patient’s right to distributive justice

The research team were concerned that because ICU clinical staff cannot be blinded to when the intervention is available, a non-structured approach to appointment allocation risks unconscious bias from staff. While a departure from BAU, simple randomisation would ensure that patients’ rights to equal opportunity in care and to participate in research is respected.

Respect the patient’s right to sufficient opportunity to consider participation prior to consent

In BAU, participants are invited to attend the post-ICU clinic via telephone several weeks after discharge. The research team felt that invitation to participate, or even to randomisation in this setting would not provide the patient sufficient time to reflect and seek advice before making a decision.

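### The protocol gives two randomisation methods and four accounts of when randomisation happens; they cannot all be followed, and some fix the arm before written consent and baseline

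*Protocol*

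**What the plan says.** On the method:

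- Protocol, Sampling and recruitment: "Patients who consent to participate will be randomised using a simple randomisation schedule".
- Protocol, Study procedure: "participants will be randomised to attend the clinic either when the psychiatrist is present or absent block randomisation in blocks of 4 or 6", at 1:1, from a list made by the study statistician and held in envelopes.
- Protocol, Ethical Considerations, Consent: "The research team decided for simple randomisation prior to consent for the following reasons".

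On the timing:

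- Sampling and recruitment describes patients who are told about the trial once standard clinic care is finished: "People who agree to participate will complete the written consent form before any data collection takes place". Randomisation then follows consent. Witnessed verbal consent is allowed for those attending by phone. The same section says "Potential participants will not be aware if they have been randomised to the control or intervention arm at this stage", wording that leaves room for randomisation to have happened already.
- The Study procedure text randomises after verbal consent, to a visit with or without the psychiatrist. It continues: "Full written consent will then be obtained when they attend their appointment". The envelopes conceal the arm only up to verbal consent.
- The time-point table in Study procedure lists consent, the initial survey and randomisation together at the clinic appointment.
- The Consent section places randomisation before consent and gives three reasons.

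Two other statements bear on this. The intervention section (General Assessment) has the intervention group attend when the psychiatrist is there. The Consent section accepts that clinical staff cannot be blinded to when the intervention is available. The planned size is about 30, "with 15 randomised to the control and intervention arms respectively".

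**The concern.** An ethics committee that reads the Consent section and a coordinator who works from Study procedure would approve and run different trials. The differences matter for bias.

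If the arm is fixed before written consent, written consent becomes a second decision taken after allocation. Patients allocated to a psychiatric review may then refuse for a reason that controls do not face. Those who remain are no longer two randomised groups. The primary analysis, a t-test of the Post Appointment Questionnaire score, uses no baseline covariate but is exposed to this selection. Two other rules could add to it: consenters without baseline or 6-month data are excluded, and the data of withdrawn participants are removed.

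The secondary outcomes are analysed by ANCOVA with the baseline value as covariate. If self-reported baselines are given after the arm is known, that covariate may itself depend on the arm. The planned comparison of baseline characteristics as a check on randomisation would also be hard to interpret.

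**Working it through.** **Step 1: the passages side by side.**

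| Place in the protocol | Method | When randomised |
|---|---|---|
| Sampling and recruitment | Simple | After consent, at the clinic |
| Study procedure, text | Blocks of 4 or 6, 1:1 | After verbal consent, before the visit and before written consent |
| Study procedure, table | Not stated | At the appointment, listed with consent and initial survey |
| Ethical Considerations, Consent | Simple | Before consent |

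The methods are mutually exclusive. On timing, the first and third rows can be read together. Neither fits the second or fourth, and those two do not fit each other.

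**Step 2: what day-based attendance implies.** If the intervention group attends on a psychiatrist day because of its allocation, allocation must precede the appointment. The table, which places randomisation at the appointment, then cannot be followed. This holds whether or not the items in that table cell are meant in sequence.

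**Step 3: who knows the arm, and when.** Under the Study procedure text, concealment ends at verbal consent. Under the Consent section, allocation precedes any consent. In both, staff know which sessions have the psychiatrist before written consent is sought.

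The baseline measures come at or after the visit:

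- HADS and EQ-5D-5L are routine assessments within standard clinic care.
- PCL-5, the self-efficacy scale and the employment questionnaire come in the initial survey, after the standard appointment.

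All of these therefore follow allocation in these two sequences.

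**Step 4: does the method matter for the planned split?** Inputs: N = 30 and 15 per arm (Participants and sample calculation).

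Simple randomisation, X ~ Binomial(30, 0.5):

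- P(15/15) = C(30,15)/2^30 = 155,117,520/1,073,741,824 = 0.144
- P(18/12 or worse) = P(X ≤ 12) + P(X ≥ 18) = 0.362
- P(20/10 or worse) = P(X ≤ 10) + P(X ≥ 20) = 0.099

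Blocks of 4 or 6: block sizes are even and 30 is even, so an unfinished last block holds 2 or 4 patients. It splits at worst 2–0 or 3–1, a difference of 2, so 16/14 is the worst result. In 200,000 simulated lists, with the two sizes assumed equally likely (the protocol does not say how they are chosen), 15/15 occurred in 77.3% and 16/14 in 22.7%.

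**Step 5: what imbalance costs.** With equal variances, efficiency relative to an even split is 4p(1 − p), where p is the share in one arm:

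- 18/12: 4 × 0.6 × 0.4 = 0.96
- 20/10: 4 × (2/3) × (1/3) = 0.89

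The stated split fits the blocked method, but the loss under simple randomisation would be small.

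**The case against.** The strongest reply is that this is loose wording in a small feasibility pilot, and that little harm is shown. Parts of it stand.

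- **Disclosure to patients.** A reader might infer that patients are told their arm before written consent. No passage says so, and Sampling and recruitment says that they are unaware at that stage. Early knowledge is clear for staff. For patients it is only a possibility, because attending on a psychiatrist day may reveal the arm.
- **Baselines.** A reader might infer that the initial survey supplies every ANCOVA baseline, or that the primary analysis depends on one. HADS and EQ-5D-5L come from routine clinic care, ANCOVA serves the secondary outcomes only, and the primary t-test uses no baseline.
- **Telephone consent.** The Consent section argues that a telephone invitation leaves too little time to decide, which appears to contradict verbal consent before the visit. That this verbal consent is taken by telephone is plausible, since Setting says first contact is by phone, but Study procedure does not say it.
- **Imbalance.** The sample is approximate, no power is stated, and 18/12 keeps 96% of the efficiency. The binomial figures are supporting evidence only.
- **A stronger remedy.** One might want the envelope opened only after the survey, with the psychiatrist booked separately. The clinic runs on Wednesdays only, and the intervention is designed to follow standard care at the same visit. Separate booking would alter the intervention, the practicability under test, and possibly the timing of the primary questionnaire between arms.

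Pilot status does not answer the conflict itself. Reading 'simple' as loose wording would leave the timing unresolved.

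**Conclusion.** The concern holds as a contradiction in the current text, in both method and timing, and should be settled before enrolment, because selection after allocation cannot be undone in the analysis. The conflict rests on the wording alone and needs no assumption.

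The consequence is a risk of unknown size. The protocol gives no refusal rate at written consent and does not say whether those who refuse are replaced, so no figure can be put on the selection. The risk to the primary outcome is through who remains in each arm. The risk through baselines concerns only the secondary ANCOVA, and for patients it depends on whether they infer their arm from the clinic day. The documents do not support saying that the arm is disclosed to patients before consent.

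**What to change.** 1. Keep the statistician's 1:1 list in blocks of 4 or 6, and delete 'simple' in Sampling and recruitment and in the Consent section.
2. State one order in Sampling and recruitment, Study procedure (text and table), the intervention section and the Consent section. Full consent, written or the witnessed verbal form already allowed for phone attendees, is complete before the envelope is opened and the clinic day is booked.
3. Where feasible, have the research-only self-report measures (such as PCL-5, self-efficacy and employment) completed before the arm is known.
4. Rewrite the rationale in the Consent section to match, including how patients get enough time to decide before the visit.
5. Count everyone whose envelope is opened in the participant flow and, where data are available, in the analysis by allocated arm.

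The cost is an amendment to protocol and ethics wording, plus one small operational burden: consent paperwork has to be completed before the clinic visit. The list, the envelopes and the same-visit psychiatric review stay as planned.
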